#### Exclusion criteria

General practices will be excluded if the practice principal or practice manager refuses participation.

General practitioners will be excluded if they work at more than one of the general practices included in the trial.

Patients will be excluded from both cohorts 1 and 2 if, within the two-year period prior to the start of the intervention, the patient record has a coded diagnosis of dementia or contains free text indicating dementia (*e*.*g*., Alzheimer’s, senility, dementia). Patients with dementia will be excluded since only GPs’ detection and diagnosis (not management) behaviours of dementia can be measured through patient medical records.

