The search module will be run nine months after the start of the intervention (delivery of a workshop), and will search the medical records over the previous three years. From the extracted data, two cohorts of patients will be identified. The first cohort (cohort 1) will include all patients aged 70 years and older at baseline (June 22, 2012), but without a diagnosis of dementia. The second, and primary cohort of interest (cohort 2), will include the subset of cohort 1 patients for whom the GP has noted a suspicion of cognitive impairment in the medical records in the period prior to intervention delivery (prior to June 22, 2012). These patients will be identified through coded fields (*e*.*g*., coded diagnosis of cognitive impairment) and review of free text entries. Two researchers (with healthcare qualifications), who are blind to the intervention group, will independently review the free text entries. Disagreements will be resolved via discussion with a geriatrician who will not be informed of the group allocation of the patient.

The different cohorts will be used to examine GPs’ clinical behaviour with all older people (cohort 1) and with those patients whom the GP previously suspected of having cognitive impairment (cohort 2). Inclusion of the former cohort allows examination of whether the intervention is effective in raising GPs’ awareness and diagnosis of cognitive impairment and dementia in all older patients (including those with and without previously noted cognitive impairment).

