#### Timing of recruitment, intervention delivery, and follow-up

The intervention educational workshop took place on the June 23, 2012. The guidelines were sent to the control group GPs in November 2012. Questionnaires measuring predictors of GPs’ detection, diagnosis, and management behaviours were collected at baseline and will be collected nine months post the educational workshop (April 2013). The cohort of patients meeting the inclusion criteria for the trial, and GPs’ detection and diagnosis behaviours of these patients, will be identified and measured via the CAT nine months post the educational workshop (from April 2013). Figure 1 depicts the timing of recruitment, intervention delivery, and follow-up.

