### Outcome measurement

Table 4 provides a summary of the measurement tools. In brief, GPs’ detection and diagnostic behaviours will be measured through the CAT where possible. Proxy measures and mediators of GP behaviour will be measured through a paper-based questionnaire (available in Additional file 1 - IRIS behavioural construct questionnaire).

**Table 4 T4:** Summary of measurement tools

**Outcome or category of outcomes**	**Measurement tool**	**Details**
*GP behaviour*		
Cognitive assessment using MMSE	CAT electronic search^†^	MMSE results recorded in the patient file or free text indicates an MMSE has been undertaken.
Depression assessment using validated scale	CAT electronic search^†^	Geriatric Depression Scale (GDS) results recorded in the patient file or free text indicates GDS, Hamilton Rating Scale for Depression, Even Briefer Assessment Scale for Depression has been undertaken.
Referral to CDAMS or specialist	CAT electronic search^†^	Free text indicates that the patient has been referred to CDAMS, ACAS (Aged Care Assessment Service), or a geriatrician.
Referral for CT scan	CAT electronic search^†^	CT scan has been requested or free text indicates that a CT (head) scan has been requested/undertaken.
Dementia diagnosis	CAT electronic search^†^	Coded diagnosis of dementia or free text indicates that the patient has dementia or Alzheimer’s disease.
Cognitive assessment using MMSE (all patients aged 70+ years)	CAT electronic search^†^	MMSE results recorded in the patient file or free text indicates an MMSE has been undertaken.
Reported suspicion of cognitive impairment (all patients aged 70+ years)	CAT electronic search^†^	Coded diagnosis of cognitive impairment or free text indicates a suspicion of cognitive impairment (*e*.*g*., confusion, muddled, cognitive), or; MMSE undertaken in isolation of the 75+ Health Check (an indication of GP’s suspicion of cognitive impairment), or; MMSE undertaken as part of 75+ Health Check with score indicating cognitive impairment (*i*.*e*., a score between 10 and 24).
Dementia diagnosis (all patients aged 70+ years)	CAT electronic search^†^	Coded diagnosis of dementia or free text indicates that the patient has dementia or Alzheimer’s disease.
*Proxy measures of GP behaviour*		

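### The dementia exclusion looks back only two years, so a patient with an older recorded dementia can enter the cohorts and be scored as a new diagnosis in the secondary outcomes

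*Protocol article*

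**What the plan says.** The article describes who counts as free of dementia in two places, and the outcome in a third.

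- **Identification of patients.** Cohort 1 "will include all patients aged 70 years and older at baseline (June 22, 2012), but without a diagnosis of dementia". No look-back period is attached. Cohort 2 is a subset of cohort 1. The search run at nine months "will search the medical records over the previous three years".
- **Exclusion criteria.** A patient leaves both cohorts if "within the two-year period prior to the start of the intervention, the patient record has a coded diagnosis of dementia". Free text counts too, the full trigger being a "coded diagnosis of dementia or contains free text indicating dementia". The reason given opens "Patients with dementia will be excluded since only GPs" and has no time limit: only detection and diagnosis can be measured from records, not management.
- **Outcome measurement, Table 4.** Dementia diagnosis is scored as "Coded diagnosis of dementia or free text indicates that the patient has dementia" or Alzheimer's disease. The wording is the same for cohort 2 and for all patients aged 70 and over. Footnote 2 to Table 2 sets the periods as the two years before randomisation and the nine months after the workshop.

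Nothing says that the entry must be the patient's first.

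**The concern.** The operative exclusion is narrower than both the cohort definition and the stated reason for excluding. Someone whose dementia was recorded only before mid-2010 meets every inclusion criterion for cohort 1 and is not caught by the exclusion. If the GP then records dementia again during follow-up, the outcome rule scores an event, although nothing was newly detected.

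The article says these outcomes measure whether the workshop raises awareness and diagnosis of dementia. Re-recording a known condition is neither. A background of such events pulls a ratio measure towards 1. If re-recording were more common in workshop practices, it would instead look like an effect. At stake are the two secondary dementia-diagnosis outcomes (cohorts 1 and 2).

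**Working it through.** **1. Who can carry over.** All of the following must hold: dementia was entered before the window; there was no code and no free-text dementia term for the two years before the workshop; the patient was active (at least three visits in the two years before follow-up) and visited during follow-up; and dementia was recorded again in the nine months. Cohort 2 also needs a recorded suspicion, or a qualifying MMSE, in those same two years. The GP would have had to document a cognitive concern in a known case without using a dementia term, so that route is narrower.

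**2. How far the extract reaches.** The Timing section states that "The intervention educational workshop took place on the June 23, 2012" and that extraction runs from April 2013. I take run dates from 23 March 2013 (nine months to the day) to 30 April 2013.

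- Search start, three years earlier: 23 March to 30 April 2010.
- Start of the two-year window: 23 June 2010.
- Extra reach: 92 to 54 days, or 3.0 to 1.8 months. Total look-back before the workshop is 27.0 to 25.8 months. A later run gains less.

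The extract therefore closes little of the gap, unless coded diagnoses are pulled regardless of date. The article does not say whether they are.

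**3. Sample size.** The stated figure reproduces: 227 per arm (50% v 65%, 90% power, two-sided 5%); design effect 1 + ((0.7² + 1) × 20 − 1) × 0.10 = 3.88; 227 × 3.88 / 20 = 44.04, rounded up to 45; 45 / 0.75 = 60 practices. It concerns the primary outcomes, and nothing here changes it.

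**4. Illustration of size (cohort 1).** Only the prevalence P comes from the document: 4.19% to 8.5%, a worldwide range for ages 60 and over given in the Background. It stands in for recorded dementia at 70 and over. The rest is assumed:

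- u: share of known cases with no dementia entry in the two years, 2% to 20%
- r: share of those re-recorded in nine months, 30% to 70%
- I: true new diagnoses in nine months, 1% to 2%
- true risk ratio 1.5, with equal re-recording in both arms

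Formulas: f = P × u × r; n = I × (1 − P); carried-over cases as a share of the cohort = f / (1 − P(1 − u)); share of counted diagnoses = f / (f + n); observed risk ratio = (f + 1.5n) / (f + n).

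| P | u | r | I | Carried over, % of cohort | % of counted diagnoses | Observed risk ratio |
|---|---|---|---|---|---|---|
| 4.19% | 2% | 30% | 2% | 0.026 | 1.3 | 1.49 |
| 4.19% | 5% | 30% | 2% | 0.065 | 3.2 | 1.48 |
| 8.5% | 5% | 70% | 1% | 0.324 | 24.5 | 1.38 |
| 8.5% | 20% | 70% | 1% | 1.277 | 56.5 | 1.22 |

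Last row: f = 0.085 × 0.20 × 0.70 = 0.0119; n = 0.01 × 0.915 = 0.00915; 0.0119 / 0.02105 = 56.5%; (0.0119 + 0.013725) / 0.02105 = 1.22.

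The planned odds ratio behaves much like the risk ratio at such low rates. The risk difference, also planned, barely moves under equal re-recording. In the last row the excess is 0.004575 either way, so it goes from 0.004575 / 0.915 = 0.50 to 0.004575 / 0.932 = 0.49 percentage points.

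**5. Unequal re-recording.** Assume no true effect, 1% new diagnoses in each arm, and re-recording in 0.3% (control) and 0.5% (intervention). The risk ratio is then 1.5 / 1.3 = 1.15. This shows only that inflation is possible.

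**The case against.** The strongest reply has four parts.

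*The text can be read more kindly.* A record that has a coded diagnosis within two years may mean a code standing in the record during that time, not one first dated in it. That reading agrees with the cohort 1 definition. It stands as a possible reading, but it shows ambiguity and does not settle the rule. It also does not cover an older diagnosis held only in free text.

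*The leak is narrow.* A reader might infer that older diagnoses in general stay in both cohorts. The documents do not support that: any dementia code or dementia text in the two years removes the patient, whenever the diagnosis was first made. This part stands in full.

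*Blinded review.* Two researchers unaware of allocation decide from free text whether the behaviour occurred, with a geriatrician to resolve disagreements. This may screen out some plainly historical mentions. But extracts are at most 40 characters, which the article admits makes coding hard, and no rule tells coders to separate known from new dementia.

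*Direction.* A reader might infer that the error inflates the workshop's effect. That needs more re-recording in the intervention arm, and there are no data on it. It is plausible: GPs are not blind, and Table 1 includes reinforcing an existing dementia diagnosis among the trial's recommendations. Blinded coding cannot undo what an unblinded GP writes. But with equal re-recording the ratio is diluted, which is the opposite direction.

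**Conclusion.** The point holds in a limited form. The exclusion rule and the cohort 1 definition disagree on time, and the outcome does not require a first entry. A known older case can therefore be counted as a new diagnosis.

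- **Where it matters:** the secondary dementia-diagnosis outcomes, mainly in cohort 1 and less often in cohort 2.
- **Direction:** dilution of the odds ratio if re-recording is equal between arms; possible inflation if the workshop prompts it. The documents do not show which.
- **Size:** not determinable. The illustration runs from about 1% to 57% of counted diagnoses, and from about 3% to 25% if 5% of known cases go unrecorded for two years. A range that wide reflects its assumptions and is not an estimate.
- **Not affected:** the sample size.

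A reader might also infer that the primary outcomes are compromised. Some known cases could enter cohort 2 and have an MMSE or depression assessment counted. But the route is narrow, the exclusion uses pre-workshop records only and is the same in both arms, and the two outcome definitions do not depend on dementia being new. I expect any effect there to be small, although the documents do not let it be quantified.

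**What to change.** 1. Reconcile the Identification of patients and Exclusion criteria sections. Exclude any patient with a coded dementia diagnosis dated before baseline (22 June 2012), however old, as far as the extract allows. Also exclude any patient with dementia free text anywhere in the extract before that date.
2. Define the dementia-diagnosis outcome in both cohorts as the first recorded dementia diagnosis, falling in the nine months after the workshop. Add to the coding dictionary a rule for entries that refer to an earlier diagnosis.
3. Establish whether the search returns coded diagnoses regardless of date. If it does, step 1 is a change of filter. If it is bound by the three-year search, step 1 gains only about two to three months. The remaining carry-over should then be stated as a limitation of these outcomes.

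The cost is slightly smaller cohorts. Changing the search module itself would cost more, because the article reports that patient-level collection had just begun. Steps 1 and 2 can be settled without reference to allocation.

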### Randomisation and allocation concealment

General practices meeting the inclusion criteria will be randomly allocated to the intervention or control groups. Restricted randomisation will be used to reduce the probability of baseline imbalance in factors thought to be predictive of the outcomes, and for potential gain in statistical power [38]. Four strata will be defined by geographical location of the practice (rural or metropolitan area) and the number of GPs per practice (<6 GPs and ≥6 GPs per practice). Geographical location may explain variation in some of the health service utilisation outcomes (*e*.*g*., imaging and specialist services), because of geographic proximity to services and geographic variation in socioeconomic status [39]. Cluster size (in our trial measured by the number of GPs per practice) is commonly employed as a stratification variable in cluster trials since it is often considered a proxy for characteristics of the cluster that may be predictive of the outcomes (*e*.*g*., educational environment within the practice) [35,38].

Within stratum, practices will be randomised with equal probability (1:1 ratio) to the intervention and control groups using computer-generated random numbers. Practices will be randomised at the same time by a statistician independent of the trial team. The statistician will be provided with a file containing only practice identification codes and stratification variables. Thus, the statistician will be provided with no identifying information.

### Blinding

The investigators will not be blind to group allocation since they will be involved in the delivery of the intervention. An exception to this is the trial statistician ([name]), who will be blinded to group allocation. Due to the nature of the intervention, GPs will not be blind to group allocation. General practitioners will be informed through recruitment information that they will be randomly allocated to receive access to materials about the detection, diagnosis and management of dementia, or a face-to-face workshop and access to materials. Self-report questionnaires completed by GPs will be entered by trial personnel who are blind to group allocation. Detection and diagnosis outcomes will be collected via the execution of a computer script (by general practice personnel) that extracts de-identified data from the practices’ electronic medical records.

### Interventions

#### Control group

The control group will receive a printed copy of the SIGN guideline for the management of patients with dementia [3].

#### Intervention group

In addition to receipt of the printed guideline, the GPs randomised to the intervention arm will receive an intervention designed to address the barriers to and enablers of implementation of the evidence-based recommendations. In phase one of this project, interviews were conducted with GPs in Victoria, Australia, underpinned by the Theoretical Domains Framework [40], a framework grounded in behavioural theory. The interviews were analysed using content and thematic analysis to identify the barriers and enablers relevant to each of the clinical behaviours. For example, the main factors identified as barriers to assessing cognitive function using a validated scale included negative beliefs about formal cognitive testing and the scales themselves (Beliefs about consequences); discomfort in administering the tests (Emotion); (possibly due to) limited training and confidence in using them (Skills, Beliefs about capabilities); limited access to tests or time and resources to undertake formal cognitive testing (Environmental context and resources); and patients finding testing uncomfortable or patients/family refusing testing (Social influences). The main factors enabling formal cognitive assessment included having an awareness of the need to undertake the assessment (Knowledge); possessing the necessary skills and confidence to do so (Skills; Beliefs about capabilities); and adequate time and resources (Environmental context and resources).

The intervention is an interactive, educational face-to-face workshop, led by an Australian geriatrician with expertise in dementia. The content of the workshop was designed using an intervention mapping process where the research team chose behaviour change techniques to address barriers/enablers within theoretical domains [24,41]. The behaviour change techniques delivered during the workshop will include: Information provision; Persuasive communication; Information regarding behaviour, outcome; Feedback; Social processes of encouragement, pressure, support; Self-monitoring; Modelling/ demonstration of behaviour by others; Increasing skills; Coping skills; Rehearsal of relevant skills; and Action planning. The workshop will be a combination of didactic presentations given by opinion leaders, and small group discussions led by trained facilitators.

#### Intervention fidelity

We plan to evaluate the fidelity of delivery of the intervention to assess the extent to which the intervention is delivered as planned [42]. The intervention workshops will be audio and video recorded, and these recordings will be analysed to determine which elements of the planned intervention were actually delivered.

#### Timing of recruitment, intervention delivery, and follow-up

The intervention educational workshop took place on the June 23, 2012. The guidelines were sent to the control group GPs in November 2012. Questionnaires measuring predictors of GPs’ detection, diagnosis, and management behaviours were collected at baseline and will be collected nine months post the educational workshop (April 2013). The cohort of patients meeting the inclusion criteria for the trial, and GPs’ detection and diagnosis behaviours of these patients, will be identified and measured via the CAT nine months post the educational workshop (from April 2013). Figure 1 depicts the timing of recruitment, intervention delivery, and follow-up.

**Figure 1 F1:**
[figure not shown]
Timing of recruitment, intervention delivery, follow-up of practitioner participants and patients.

### Study outcomes

#### Primary outcomes

The primary outcomes (cognitive assessment using MMSE, depression assessment using validated scale) provide measures of whether the GPs undertake a formal assessment for cognitive impairment and depression (Table 2). These behaviours have been selected since they reflect the two key recommendations from the SIGN guideline [3] (with level B evidence) that have identified evidence-practice gaps and have the potential to be implemented into practice through behaviour change (*i*.*e*., there are no structural barriers to the implementation of the practice). In addition, these behaviours can be objectively measured through the CAT.

**Table 2 T2:** Outcome measures

**Outcome**	**Data collection method**	**Outcome assessment period**	**Source**	**Level data collected**
**Primary outcomes**				
*GP behaviour*				
Cognitive assessment using MMSE^1*^	Clinical Audit Tool (CAT) electronic search	Baseline & 9 months post workshop delivery^2^	Medical record	Patient
Depression assessment using validated scale^1*^	CAT electronic search	Baseline & 9 months post workshop delivery^2^	Medical record	Patient
**Secondary outcomes**				
*GP behaviour*				
Referral to CDAMS or specialist^1†^	CAT electronic search	Baseline & 9 months post workshop delivery^2^	Medical record	Patient
Referral for CT scan^1*^	CAT electronic search	Baseline & 9 months post workshop delivery^2^	Medical record	Patient
Dementia Diagnosis^1^	CAT electronic search	Baseline & 9 months post workshop delivery^2^	Medical record	Patient
Cognitive assessment using MMSE (all patients aged 70+ years)^3*^	CAT electronic search	Baseline & 9 months post workshop delivery^2^	Medical record	Patient
Reported suspicion of cognitive impairment (all patients aged 70+ years)^3^	CAT electronic search	Baseline & 9 months post workshop delivery^2^	Medical record	Patient
Dementia diagnosis (all patients aged 70+ years)^3^	CAT electronic search	Baseline & 9 months post workshop delivery^2^	Medical record	Patient
*Proxy measures of GP behaviour*				
Self-report of adherence to recommended behaviours:	Questionnaire	Baseline & 9 months post workshop delivery	Practitioner	Practitioner
Cognitive assessment using MMSE*	(1 item each)			
Depression assessment using validated scale*				
Referral to CDAMS or specialist^†^				
Referral for CT scan*				
Review of medications^§^				
Ordering of pathology tests^‡§^				
Behavioural simulation to adhere to recommended behaviours:	Questionnaire (clinical vignettes)	9 months post workshop delivery	Practitioner	Practitioner
Cognitive assessment using MMSE*				
Depression assessment using validated scale*				
Referral to CDAMS or specialist†				
Referral for CT scan*				
Review of medications§				
Ordering of pathology tests‡§				
Disclosure of diagnosis to patient‡§				
Disclosure of diagnosis to carer‡§				
*Hypothesised mediators of GP behaviour*				
Intention to adhere to recommended behaviours:	Questionnaire	Baseline & 9 months post workshop delivery	Practitioner	Practitioner
Cognitive assessment using MMSE*	(3 items)			
Depression assessment using validated scale*	(3 items)			
Disclosure of diagnosis to patient‡§	(6 items)			
Disclosure of diagnosis to carer‡§	(2 items)			
Behavioural constructs for primary outcomes^4^	Questionnaire	Baseline & 9 months post workshop delivery	Practitioner	Practitioner
	(47 items)			

Symbols indicate source of recommended behaviour: * SIGN guideline; † Local adaptation of SIGN guideline (by IRIS clinical investigators); ‡ Other guidelines; § Considered best practice by the IRIS clinical investigators.

^1^Active patients aged 70 years and over in whom the GP suspects cognitive impairment at baseline (cohort 2). Active is defined as a minimum of three visits recorded in the general practice clinical desktop system in the two-year period preceding follow-up (nine months post workshop delivery)).

^2^For this variable, the outcome is measured over the two-year period prior to randomisation and nine months post workshop delivery.

^3^Active patients aged 70 years and older (cohort 1). See footnote 1 for the definition of active.

^4^Table 3 provides details of behavioural construct domains for the primary outcomes.

